## Abstract

**Background and objectives:**

Spinal cord injury (SCI) often results in permanent paralysis, leading to substantial long-term disability and loss of quality-adjusted life years. Strategies to preserve neural function in the hyperacute phase are needed. Transcutaneous spinal cord stimulation (tSCS) improves neurological function in chronic SCI. Earlier implementation in acute SCI may preserve or restore function and improve recovery.

**Methods:**

STEP-RAISE is a Phase 1/2 prospective clinical trial evaluating the safety and preliminary efficacy of tSCS in acute moderate-to-severe traumatic SCI. Electrical current will be delivered to the lumbosacral spinal cord using the investigational ARC-Ex device (ONWARD Medical) via surface electrodes over the thoracolumbar region. Phase 2 is a randomized, triple-blinded, placebo-controlled trial designed to assess treatment effects. Safety outcomes include hemodynamics, spinal cord perfusion pressure, and skin reactions. Efficacy will be assessed using the International Standards for Neurological Classification of Spinal Cord Injury (ISNCSCI) examination with electromyography at baseline, during stimulation, and at 6-month follow-up. Biomarkers include neuronal (UCH-L1) and glial (GFAP) markers and exploratory proteomics in blood and cerebrospinal fluid collected prior to stimulation and at discharge.

**Discussion:**

The STEP-RAISE trial evaluates safety and preliminary efficacy of non-invasive tSCS initiated within 72 h of SCI to improve sensorimotor recovery. Neurophysiological and patient-reported outcomes will characterize recovery and assess whether early tSCS augments functional recovery. This study is designed to estimate treatment effects and inform subsequent trials in acute SCI. Planned enrollment includes 5 participants in Phase 1 and 10 in Phase 2.

**Clinical trial registration:**

ClinicalTrial.gov: NCT07090473; first posted on 07/29/2025, first open to enrollment 04/2026. https://clinicaltrials.gov/study/NCT07090473

## Introduction

### Background and rationale

Spinal cord injury (SCI) is a severe neurologic condition for which no established neuroprotective therapy exists in the acute phase. In the United States, more than 100,000 individuals sustain SCI each year, and over 2 million people live with chronic disability related to these injuries (Safdarian et al., 2023). Acute SCI (aSCI) commonly leads to persistent motor, sensory, and autonomic impairments, resulting in substantial long-term morbidity and societal burden. Current acute management is largely supportive and includes surgical decompression and maintenance of adequate spinal cord perfusion (Shank et al., 2019; Karsy and Hawryluk, 2019). Pharmacologic strategies such as high-dose corticosteroids remain controversial and are used inconsistently (Pointillart et al., 2000; Matsumoto et al., 2001). Despite early rehabilitation, recovery of voluntary movement below the level of injury is often limited. Patients are also vulnerable to systemic complications related to immobility and autonomic dysfunction, including cardiovascular instability (Wecht et al., 2020), immune dysregulation (Schwab et al., 2014), and respiratory impairment (Rosales-Antequera et al., 2022). The initial hospitalization, lasting 11 days on average, represents a unique window during which secondary injury processes and physiologic deconditioning may further worsen outcomes (Team, S. C., 2023).

There is, therefore, a significant unmet need for interventions that can be initiated early after injury to preserve neural function and mitigate downstream complications. Electrical stimulation has been investigated as a potential neurotherapeutic strategy in SCI. In preclinical models, externally applied electric fields influence axonal orientation and cellular behavior (Marsh and Beams, 1946; Patel and Poo, 1982). Studies using oscillating field stimulation applied directly to injured spinal cord tissue have demonstrated improved locomotor recovery in animals, associated with greater tissue preservation, enhanced oligodendrocyte survival and differentiation, axonal remyelination, and reduced glial scar formation (Bacova et al., 2022; Zhang et al., 2015). These findings suggest that electrical stimulation can modulate biological processes relevant to secondary injury.

Activity-patterned stimulation paradigms further indicate that electrical input may influence network-level physiology after trauma (Taccola et al., 2020). In rodent models of acute contusion SCI, stimulation designed to approximate physiological sensorimotor activity has been associated with restoration of motor-evoked potentials compared with sham stimulation (Taccola et al., 2020). Although mechanisms remain incompletely defined, proposed effects include stabilization of network excitability and activity-dependent neurotrophic signaling (Taccola et al., 2020). Collectively, preclinical data support the premise that electrical stimulation can alter both cellular and circuit-level responses after SCI.

Only limited pilot studies in humans after acute SCI with implanted stimulators demonstrate safety and signs of potential efficacy (Shapiro et al., 2005). Clinical translation of spinal cord stimulation has advanced most in chronic SCI. Epidural lumbosacral stimulation has enabled recovery of sensorimotor and some autonomic functions in selected individuals with longstanding paralysis, demonstrating that spinal networks below the lesion retain capacity for functional modulation (Aslan et al., 2018; Harkema et al., 2011; Angeli et al., 2014; Calvert et al., 2026; Phillips et al., 2025; Shackleton et al., 2023; Singh et al., 2023). Non-invasive transcutaneous spinal cord stimulation (tSCS), delivered through surface electrodes, avoids surgical implantation, and has been associated with improvements in motor performance, trunk control, and standing or stepping ability when combined with rehabilitation in chronic SCI (Inanici et al., 2021; Gerasimenko et al., 2015; Sayenko et al., 2019; Rath et al., 2018). A proposed mechanism is increased excitability of lumbosacral spinal networks, enhancing responsiveness to residual descending and sensory inputs (Gerasimenko et al., 2015).

tSCS has demonstrated a favorable safety and tolerability profile in rehabilitation settings, including pediatric populations (Keller et al., 2021; Amirova et al., 2025; Lucas et al., 2025; Singh et al., 2024). Its non-invasive nature, feasibility, and physiological effects make it a candidate intervention for earlier use after injury. Based on preclinical evidence and clinical data from chronic SCI, we designed a clinical trial to evaluate whether non-invasive lumbosacral tSCS applied distal to the lesion site may be safely initiated during acute hospitalization after SCI and show signals of biological and functional impact, with the goal of informing strategies to improve neurologic recovery trajectories.

### Objectives

This study has three main objectives. First, test the safety of tSCS applied below the level of injury to the lumbosacral spinal cord after acute spinal cord injury, starting 72 h after injury. We hypothesize that there will be no adverse events associated with acute application of tSCS. Second, demonstrate the proof-of-principle that tSCS application in the acute phase post-injury can potentiate recovery. We hypothesize that tSCS can improve volitional movement and/or sensation acutely after SCI as measured by an improved lower extremity motor score in the presence of tSCS. Third, identify treatment-related mechanistic biomarkers (exploratory). We hypothesize that there will be fluid-based biomarkers that will change in the setting of tSCS receipt.

## Methods

### Patient and public involvement

In accordance with Congressionally Directed Medical Research Programs (CDMRP) requirements, two individuals with lived experience with SCI were invited to serve as community representatives for this clinical trial. Their feedback was solicited to inform study execution. The study design, protocol, and informed consent materials were reviewed and discussed during a dedicated meeting and shared with the community representatives to incorporate their input.

### Trial design

We will conduct a Phase 1 and Phase 2 clinical trial (Figure 1). Phase 1 is an open label study focused on determining safety of the initial 60 min of tSCS between 72 and 96 h after spinal cord injury (*n* = 5). Phase 2 is a randomized, placebo-controlled triple-blinded clinical trial with a parallel group assignment (active tSCS, *n* = 5 and sham tSCS *n* = 5) focused on determining safety and efficacy of tSCS for treatment of acute SCI. A total of 15 subjects will be enrolled across Phase 1 and Phase 2. A sham-controlled design was selected to isolate the physiological effects of electrical stimulation from nonspecific influences related to device application, participant expectations, investigator interaction, and increased clinical monitoring.

**Figure 1 fig1:**
[figure not shown]
Study design and transcutaneous spinal cord stimulation paradigm in acute spinal cord injury. Schematic representation of the two-phase clinical trial conducted in the acute spinal cord injury (SCI) setting. Phase 1 (*n* = 5) consists of an open-label safety assessment during a single 60-min tSCS application, followed by Phase 2 (*n* = 10), a randomized, participant- and assessor-blinded comparison of active versus sham transcutaneous spinal cord stimulation (tSCS). Participants are enrolled upon admission to the intensive care unit and undergo baseline assessments starting at 72 h post SCI within the first 96 h, including International Standards for Neurological Classification of Spinal Cord Injury (ISNCSCI) examination, lower extremity electromyography (EMG), motor evoked potentials, blood and cerebrospinal fluid draws for biomarker assessment, and patient-reported outcomes (PROs). In Phase 2, participants receive daily tSCS or sham stimulation at T11/L1 for 60 min for a total of 5 sessions. Continuous vital sign monitoring is performed during stimulation sessions. Follow-up assessments, including neurological, neurophysiological, and patient-reported measures, are conducted at 7 days post-injury and at 6 months for both Phase 1 and Phase 2 participants. RF—rectus femoris, BF—biceps femoris, MG—medial gastrocnemius, TA—tibialis anterior, EHL—extensor hallucis longus, DPI - days post injury.

### Trial setting

This study will be conducted in the neurotrauma intensive care unit (ICU) at Zuckerberg San Francisco General Hospital and Trauma Center (ZSFG). All patients will be admitted to the ICU, and treated per standard of care according to hospital protocol for acute SCI.

### Eligibility criteria

Patients will be screened for eligibility during the first 3 days of ICU stay based on the following eligibility criteria (Figure 2):

**Figure 2 fig2:**
[figure not shown]
Eligibility criteria. Overview of the two-phase trial inclusion and exclusion criteria and participant allocation across open-label and randomized phases.

Inclusion criteria:

A subject will be eligible for enrollment in the study if the following criteria apply:

1 Written informed consent is obtained.2 Acute traumatic cervicothoracic SCI that meets all of the following criteria:

Acute SCI presenting to the hospital within 12 h of injuryTraumatic non-penetrating SCIAIS Grade A, B, or CISNCSCI neurological level of injury between C4 and T10

3 Aged ≥18 years4 Admission to ICU

Exclusion criteria:

1 Subjects classified as AIS D or E2 Penetrating SCIs or complete transection of the spinal cord3 Pregnancy4 Incarceration or police custody5 Class 2 or Class 3 obesity6 Any concomitant injury that, in the judgment of the Investigator, interferes with the procedures and examinations required by the study protocol, including but not limited to:

Multiple spinal cord lesionsFractures requiring lower extremity casts or splintsSkin breakdown or burns over the lumbar spineProfound hemodynamic instabilityTraumatic brain injury (defined by GCS < 14 at enrollment or inability to participate in exam)

### Intervention and comparator

Transcutaneous spinal stimulation will be delivered using ARC^EX^ device (ONWARD Medical), via skin surface electrodes placed over the spine targeting lumbosacral spinal cord at T10 and L1 using round 3.2 cm in diameter stimulating electrodes, and bilaterally on the iliac crests using rectangular, 7.5 × 13 cm reference electrodes during the intervention. Based on previous studies on safety and efficacy of tSCS, we will use biphasic waveforms with a burst frequency of 30 Hz, a carrier frequency of 10 kHz, with a pulse width of 1,000 μs (Gerasimenko et al., 2015; Keller et al., 2021; Moritz et al., 2024). Stimulation will be delivered continuously for 60 min once (for Phase 1 participants) and once a day for 5 consecutive days (for Phase 2 participants). The intensity of the stimulation will be increased gradually to the motor threshold intensity (Moritz et al., 2024) and lowered until motor responses subside if there are any. Increase in trunk/lower extremity muscle tone will be additionally monitored to assess whether the amplitude of stimulation required to reach motor threshold changes with days post injury + tSCS treatment for Phase 2 participants. If stimulation does not elicit any obvious motor responses due to spinal shock, the stimulation intensity will be chosen based on previously reported ranges of effective stimulation, including those observed in our ongoing clinical trial in patients with chronic low back pain (NCT05265000) which provides ranges of maximum tolerable stimulation intensities in individuals without SCI, who have full sensation. The stimulation parameters used in that study are identical to those proposed in STEP-RAISE, including waveform, pulse width, carrier frequency, and electrode configuration, allowing for adaptation of stimulation intensities if necessary. The specific stimulation parameters and optimal stimulation intensity will be left to the discretion of the investigators during this experimental treatment. A range of the investigated stimulation parameters will be systematically recorded and will be reported as part of the methodology for each participant. The stimulation will be delivered while the participant is lying supine in the ICU bed. The lower motor ISNCSCI exam will be performed within the last 30 min of stimulation to assess whether acute tSCS potentiates volitional lower extremity movement. Although physical therapy (PT) is provided to acute SCI patients, in this trial the goal is to assess whether tSCS alone can be delivered safely, and will not be combined with the standard of care ICU PT. Participants will be continuously monitored and asked to provide any verbal feedback regarding stimulation to ensure there is no pain or discomfort during treatment.

For sham stimulation (comparator), electrodes will be placed in the same location. The participant will be continually monitored and given similar verbal cues as with the stimulation trials, but no electrical current will be delivered. Participants in both arms will be informed that they may or may not feel the stimulation.

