### Blinding

Due to the objectives of the study, the identity of test and control treatments will be known to the investigator who administers treatment but will not be known to the research staff who conduct the assessments, the participants or the ICU care team/physicians. The following study procedures will be in place to ensure single-blind administration of study treatments: (1) access to the randomization code will be strictly controlled, (2) participants will be informed that they may or may not feel the stimulation, (3) the stimulator/its settings will be hidden from the assessor, (4) all the communication between the patient and investigator who will be monitoring for safety will be kept consistent between the sham and active treatment group. The study blind will be broken on completion of the clinical study and after the study database has been locked. Unblinding prior to study completion will only occur if required for clinical safety and will be conducted by the Principal Investigator with documentation of the reason and timing.

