For ISNCSCI and neurophysiological assessment, the participant will be instrumented with 10 surface electromyography recording electrodes (Delsys, Inc), placed bilaterally over the lower extremity muscles: Rectus Femoris (RF), Biceps Femoris (BF), Medial Gastrocnemius (MG), Tibialis Anterior (TA), Extensor Hallucis Longus (EHL). Stimulating electrodes will be placed on the skin over the low thoracic, lumbar spine and the grounding electrodes will be placed over the iliac crest bilaterally. The stimulation will be delivered as single, 1-ms monophasic square-wave pulses every 6 s while patient is lying in supine. Using 2-mA increments, the stimulation intensity will be increased from 2 to 100 mA or if the participant requests to stop stimulation. Three stimuli will be delivered at each intensity. The stimulation will be delivered using an experimental Neo-Stim 5 (Cosyma, LTD) transcutaneous spinal cord stimulator, as ARC-Ex currently does not support single-pulse tSCS paradigm required to evoked discrete motor responses. Neurophysiological outcome measures will include the presence or absence of elicitable motor evoked potentials (MEPs) and the number of muscles demonstrating elicitable responses (Table 1). The neurophysiological assessment will be performed at baseline twice (before and right after the first 60 min of continuous tSCS) and at 7 days post-SCI (or at hospital discharge whichever is earlier) if the standard of care continuous vital signs monitoring is still ongoing. Frequent vital signs will be captured during tSCS for analysis and will be monitored continuously as per standard of care.

When available, clinically acquired MRI data and intraoperative MEPs obtained as part of standard care will be reviewed. MRI severity will be characterized using the Brain and Spinal Injury Center (BASIC) score and used as an exploratory descriptor of injury severity and natural recovery potential (Talbott et al., 2015; Dhall et al., 2018).

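### A zero-current sham, with the primary motor exam done during the session, puts participant and assessor blinding at risk where sensation or visible responses exist, and the blinding labels conflict

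*Protocol article*

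**What the plan says.** All references are to the protocol article.

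- **Sham** (Intervention and comparator): electrodes go in the same place, and the participant is "given similar verbal cues as with the stimulation trials, but no electrical current will be delivered". As a safeguard, "Participants in both arms will be informed that they may or may not feel the stimulation".
- **Active arm** (same section): "The intensity of the stimulation will be increased gradually to the motor threshold intensity", after which it is lowered until any motor responses subside. The section also covers the case of no visible response ("If stimulation does not elicit any obvious motor responses due to spinal shock") by taking the intensity from previously reported ranges. Participants are asked for verbal feedback on the stimulation throughout.
- **Test pulses** (Data collection methods): for the motor evoked potential assessment, "Using 2-mA increments, the stimulation intensity will be increased from 2 to 100 mA or if the participant requests to stop stimulation", with three stimuli per level, one every 6 seconds. This is done before and right after the first 60-minute session, and again at 7 days or discharge if continuous vital-sign monitoring is still running. Neither arm is exempted.
- **Exam and outcome**: the lower motor ISNCSCI exam is performed in the last half hour of stimulation to look at volitional movement (Intervention and comparator). The immediate change in lower motor score is one of two components of the Phase 2 primary efficacy outcome; the other is change from baseline to after treatment (Table 1).
- **Blinding labels**: Trial design describes a "randomized, placebo-controlled triple-blinded clinical trial", and the Abstract also says triple-blinded. The Figure 1 legend says participant- and assessor-blinded. The Blinding section says "The following study procedures will be in place to ensure single-blind administration of study treatments", although it has just listed assessors, participants and the ICU care team as blinded and the administering investigator as unblinded.

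**The concern.** Trial design says the sham arm was chosen to separate the electrical effect from expectation and attention. That works only if participants and assessors cannot tell the arms apart when the outcome is scored.

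A sham participant with sensation over the electrodes receives test pulses, then an hour with no current, then test pulses again. An active participant with sensation is likely to notice the titration and the continuous current. The motor score depends on the participant's effort and the examiner's grading, and one component of the primary outcome is scored while current is on in one arm and off in the other. If either party can guess the arm, the active-sham difference may include an expectancy effect. The Sample size section says these data will supply effect sizes for later trials, so any such bias would carry into their planning.

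**Working it through.** No stated figure is in dispute, so the check is mainly a side-by-side reading, with a count of the test pulses and two illustrations that rest on assumptions.

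**1. First treatment day, by arm**

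| Step | Active | Sham |
|---|---|---|
| Test pulses before the session | up to 100 mA | same (no arm exempted) |
| Start of session | raised to motor threshold, then lowered until responses subside | no current |
| Remainder of the 60 minutes | continuous current | no current |
| Lower motor exam, last 30 minutes | current on | current off |
| Test pulses after the session | up to 100 mA | same |

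**2. Number of test pulses** (inputs from Data collection methods)

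- Levels: 100 / 2 = 50.
- Pulses per assessment: 50 × 3 = 150.
- Duration: 150 × 6 s = 900 s = 15 minutes.
- Ceiling over three assessments: 3 × 150 = 450.

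Only the first 150 come before the first exam during stimulation. The participant may stop the ramp early, and the third assessment is conditional, so 450 is an upper limit.

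**3. Who could notice.** Eligibility covers AIS A, B or C with a neurological level from C4 to T10. Intervention and comparator places the stimulating electrodes at T10 and L1. Sensation at the electrodes will therefore vary from none to preserved, and the documents give no share.

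Assumption: each of the 5 active participants independently has probability p of feeling the current. The chance that at least one does is 1 − (1 − p)^5:

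- p = 0.2: 1 − 0.8^5 = 0.67
- p = 0.4: 1 − 0.6^5 = 0.92
- p = 0.6: 1 − 0.4^5 = 0.99
- p = 0.8: 1 − 0.2^5 > 0.99

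**4. What reaches the assessor.** The Blinding section hides the stimulator and its settings. It does not address muscle responses seen during titration, what the participant says about sensation, or the stimulation artifact in surface EMG that Data collection methods acknowledges.

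**5. Possible size of the bias.** Take bias = (share of the active arm unblinded) × (expectancy shift in SD). Both inputs are assumptions.

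- Low end: 0.40 × 0.25 = 0.10 SD.
- High end: 1.00 × 1.00 = 1.0 SD.

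As a rough yardstick, the motor-score eta squared of 0.18 in Sample size gives f = √(0.18/0.82) = 0.47 and d = 2f = 0.94. The range is then 0.10/0.94 = 11% to 1.0/0.94 = 107% of that effect. A range this wide shows only that the bias could be trivial or could match the planning effect.

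**6. Labels.** The Blinding section names three blinded parties, which fits triple-blinded. The Figure 1 wording is compatible but omits the ICU care team. Single-blind fits neither the list nor the other labels.

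**The case against.** The strongest case on the other side has five parts.

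- **Titration ends below the visible threshold.** The intensity is lowered until motor responses subside, and spinal shock may mean there are none. This stands, and it removes much of the visible cue at the exam itself. It does not remove what an assessor present during titration would have seen, or what the participant feels.
- **Safeguards exist.** Both arms are told they may or may not feel stimulation, settings are hidden, communication is kept consistent between arms, and access to the code is controlled. These count in the plan's favour. They reduce the cue for a participant with sensation but do not remove it.
- **Pulses given are not pulses felt.** A reader might infer that every participant has already felt what treatment is like. The documents do not support this: insensate participants may feel nothing, and the test pulses are single monophasic pulses from a different device, whereas treatment is a continuous biphasic burst waveform.
- **Triple-blinded is not the wrong label.** A reader might infer that it is. The list of blinded parties supports it; single-blind is the stray term.
- **Efficacy is declared exploratory.** This also stands and limits the consequence. It does not make the blinding description correct, and it does not protect effect sizes passed on to later trials.

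**Conclusion.** The point holds as a risk to blinding in a subset of participants, together with a plain contradiction in labels. Blinding is at risk for participants with preserved sensation and, through the assessor, for those with visible responses or who comment on sensation. It may hold for insensate participants.

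A reader might go further and conclude that the blind fails altogether, or that sham participants receive 450 perceptible pulses. The documents support neither: 450 is a ceiling, at most 150 precede the first exam, and perceptibility is not stated.

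The size of any bias cannot be derived from the documents. The 0.10 to 1.0 SD range rests wholly on assumed unblinding shares and expectancy effects. The direction is probably in favour of active stimulation, but that is a judgement. The change is worth making because it is nearly free and either protects or qualifies the primary efficacy contrast.

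**What to change.** 1. Use one blinding label throughout. Name the blinded parties (participants, assessors, ICU care team) and state that the investigator giving treatment is unblinded. Remove the single-blind wording.
2. Keep the assessor out of the room during titration, or its sham equivalent, in both arms. Let the unblinded investigator alone handle participants' feedback about sensation.
3. Record the participant's and the assessor's guess of arm after session 1 and at the 7-day or discharge exam, and report the guesses descriptively. Five per arm is too few to test: even 5 of 5 correct has a lower 95% limit of 0.025^(1/5) = 0.48.
4. Report the during-stimulation contrast as open to expectancy bias, beside the 7-day or discharge score, and state that the latter exam is done with current off. That score is less exposed, because the exam is not done while current differs between arms. It is not immune, because a participant who has guessed the arm still knows it.

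The cost is wording, two case report form items and minor session logistics. The stimulation regimen is unchanged. Whether sham should include any current is for the investigators and is not part of this fix.
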